### Transcranial Doppler

Transcranial Doppler imaging will be performed daily until 14 days after surgery. The mean velocity of the proximal middle cerebral artery (M1) will be recorded in both hemispheres.

### Biochemical markers

Venous blood and CSF samples will be taken for assays of several biochemical markers at 1, 3, 7, and 14 days after surgery. Malondialdehyde will be assessed as an indicator of oxidative stress [33,46]. Neuron-specific enolase and S-100 calcium binding protein B will be assessed as markers of neuronal and glial injuries [21,47]. C-reactive protein will be assessed as an inflammatory marker [21,48].

### Outcome measures

Primary outcome measures will be as follows.Occurrence of DCI: new focal neurological deficits (motor or speech deficits) that developed after SAH, decrease in Glasgow Coma Scale of ≥2 points for >6 hours, or new cerebral infarction not related to surgery, rebleeding, progressive hydrocephalus, electrolyte or metabolic disturbance, or infection [5,15].Occurrence of cerebral vasospasm: angiographic vasospasm which is defined as moderate-to-severe arterial narrowing on CT angiography and/or digital subtraction angiography not attributable to atherosclerosis, catheter-induced spasm, or vessel hypoplasia. Transcranial Doppler vasospasm which is defined as a mean flow velocity in the M1 of >120 cm/s [49].

Secondary outcome measures will be as follows.Modified Rankin scale score at 3, 6, and 12 months.Biochemical markers (malondialdehyde, neuron-specific enolase, S-100 calcium binding protein B, and C-reactive protein).

### Sample size

Assuming that the incidence of DCI is 35% in the control group, 15% in the Mg group, and 5% in the Mg + H_2_ group, a total of 413 patients will be required (80% power and 2-sided α = 0.05). However, assuming approximately 10% loss to follow up, 450 patients will need to be recruited. Therefore, 150 patients must be randomized to each intervention arm.

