### Randomization

Patients who fulfill the eligibility criteria will be assigned to either the control group, Mg group, or Mg + H_2_ group by stratified block randomization, which will be carried out using a computer system by a statistician not related to the project team to protect the double-blind design and integrity of the study. Randomization will be stratified by sex, age (20–60 years and older than 60 years), Hunt and Kosnik grade, and Fisher group. The allocation ratio will be 1:1:1. Patients, treating physicians, and investigators assessing outcomes and analyzing data will be unaware of the allocation.

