### Statistical analysis

The study design accords to the ‘intention to treat’ principle. A test for overall comparison (e.g. analysis of variance, or if the conditions for analysis of variance are not met, a non-parametric equivalence such as the Kruskal-Wallis test) will be employed for each outcome across all three interventions, and if found to be significant, pair-wise comparisons will be made. We appreciate that many pair-wise comparisons suffer from Type I (false-positive) error, so we will adjust for multiplicity of comparisons by using steps such as Bonferroni and Tukey's procedure. The statistical procedures for pair-wise comparisons will depend on the nature of the data: for example, for dichotomous outcomes, we will use Fisher’s exact test or chi-square test as appropriate, and for continuous outcomes we will use the t-test if the observations in each arm are normally distributed; or the Mann–Whitney U-test if non-normally distributed. A value of p < 0.05 will be considered significant.

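### The 413 patients give 80% power for Mg + H2 versus Mg only at an unadjusted 0.05; under the Bonferroni adjustment the analysis section names, power is about 67%

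*Protocol article*

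**What the plan says.** The Sample size section of the protocol article sets the planning rates: "Assuming that the incidence of DCI is 35% in the control group, 15% in the Mg group, and 5% in the Mg + H_2_ group". From these it concludes that "a total of 413 patients will be required (80% power and 2-sided α = 0.05"). It continues: "assuming approximately 10% loss to follow up, 450 patients will need to be recruited", and "150 patients must be randomized to each intervention arm". It does not say which of the three comparisons, or whether the overall test, produces 413, and it mentions no multiplicity adjustment.

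The Statistical analysis section starts each outcome with an overall three-arm test; "if found to be significant, pair-wise comparisons will be made". For those pairs, "we will adjust for multiplicity of comparisons by using steps such as Bonferroni and Tukey's procedure". Dichotomous outcomes are to be compared by Fisher's exact or chi-square test, whichever suits. The Outcome measures section lists two primary outcomes, DCI and cerebral vasospasm.

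**The concern.** The size calculation appears to spend the full 0.05 on one pair, while the analysis tests that pair at a smaller level. If so, the stated 80% does not describe the test that will be run.

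The loss falls on the contrast that matters most. Mg + H2 and Mg differ only in the added hydrogen, so this is the one comparison that isolates the new component. It also has the smallest assumed difference (10 percentage points) and therefore drives the sample size. At stake is the chance of missing the assumed hydrogen effect: about one in three instead of one in five.

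**Working it through.** **Inputs.** DCI rates of 35%, 15% and 5%, two-sided alpha 0.05, 80% power, 413 evaluable and 450 randomised (Sample size); 1:1:1 allocation (Randomization); three pairs after an overall test, with adjustment (Statistical analysis). Patients analysed per arm: 413/3 = 137.7, so 138; 450 x 0.9 / 3 = 135; or 150 with no loss.

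**Step 1: reproduce 413.** The unpooled two-proportion formula is

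n per arm = (z for alpha/2 + z for power)² x [p1(1 − p1) + p2(1 − p2)] / (p1 − p2)².

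- Mg vs Mg + H2: (1.960 + 0.842)² x (0.1275 + 0.0475) / 0.10² = 137.36; x 3 = 412.07, rounded up to 413.
- Control vs Mg, same formula: 69.66 per arm, 209 in total.
- Control vs Mg + H2: 23.98 per arm, 72 in total.
- Overall three-arm chi-square (2 df): 31 per arm, 93 in total.
- Mg vs Mg + H2 at 0.05/3: (2.394 + 0.842)² x 17.5 = 183.2 per arm, about 550 in total.

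Only the first matches. The pooled formula for the same pair gives 141 per arm (423), close but not exact. Rounding up per arm before multiplying gives 138 x 3 = 414.

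**Step 2: power for 15% vs 5%.** Chi-square test, exact enumeration of both binomial distributions:

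| Level per pair | 135 per arm | 138 per arm | 150 per arm |
|---|---|---|---|
| 0.05 (unadjusted) | 81% | 82% | 84% |
| 0.025 (Bonferroni, two pairs) | 71% | 72% | 76% |
| 0.0167 (Bonferroni, three pairs) | 67% | 67% | 71% |

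The normal approximation at 0.0167 is slightly lower: 64% at 135, 65% at 138 and 69% at 150. A Tukey-type level (about 0.0191 per pair) gives 67% to 68% at 138. Fisher's exact test at 0.0167 gives 57%, 59% and 64% across the three columns.

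**Step 3: the other pairs.** At 0.0167 and 138 per arm, control vs Mg has about 93% power and control vs Mg + H2 about 100%. The overall test also has almost 100%, so the gate costs nothing under the planning rates. The shortfall comes from the pairwise adjustment and is confined to one pair.

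**Step 4: alternatives.** With three arms, the only larger null hypothesis containing a given pair is equality of all three arms. An overall test at 0.05 followed by each pair at 0.05 is therefore a closed test and controls familywise error strongly over the three pairs. Simulation with 400,000 trials per scenario at 138 per arm:

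- Power for Mg + H2 vs Mg: closed test 82%, Holm 82%, gate plus single-step Bonferroni 67%. Holm loses almost nothing because the other two pairs are nearly always rejected first.
- Familywise error within DCI: closed test 0.049 to 0.050. Gate plus Bonferroni 0.040 to 0.042 when all arms are equal, and 0.016 to 0.017 when only two are equal.

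**Step 5: two primary outcomes.** Assume, for illustration, that DCI and vasospasm are independent. With two of three arms equal on both outcomes, the chance of at least one false pairwise claim is 1 − (1 − 0.016)² = 3.2% under gate plus Bonferroni and 1 − (1 − 0.05)² = 9.8% under the closed test. With all arms equal it is about 7.9% and 9.7%. Positive correlation would narrow the difference.

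**The case against.** The strongest reply is that the analysis text is open. Bonferroni and Tukey are introduced as examples, in an article that condenses a fuller plan. A step-down method such as Holm is not named but not excluded either, and it would keep about 82%. This stands: a reader might infer that the plan cannot reach 80% under any reading, and the document does not support that. What it supports is that neither named single-step method delivers the stated power.

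Other tempting inferences also fail:

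- *The adjustment is superfluous and can be dropped with no loss of error control.* True only within DCI. There are two primary outcomes and no stated adjustment across them, so the conservative pairwise step gives some incidental protection at trial level.
- *Tukey's procedure is misapplied to a binary outcome.* The section covers all outcomes, including continuous biomarkers, makes the choice depend on the type of data, and does not assign Tukey to DCI.
- *Power is below 60%.* That requires Fisher's exact test. The protocol allows chi-square where appropriate, and about 13.5 expected events per arm (10% of 135) make it so.

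Two further points stand in part. The 10% loss may hardly affect DCI, since the scheduled imaging and Doppler end at day 14; 71% is then the better figure, still short of 80%. And the sizing comparison is inferred, though no other candidate comes near 413.

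**Conclusion.** The point holds. The sample size uses an unadjusted 0.05 for Mg + H2 vs Mg, while the analysis section adjusts the same comparison. Under single-step Bonferroni over three pairs, power is about 67% at 135 to 138 per arm and about 71% at 150, a shortfall of roughly 9 to 13 percentage points from the stated 80%. Control vs Mg and control vs Mg + H2 remain above 90%.

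This rests on four assumptions: that 413 was derived from the Mg vs Mg + H2 pair, that the planning rates are right, that the chi-square test is used, and that the adjustment is one of the two single-step methods named. It is a mismatch between two sections that wording can resolve; it does not show that the trial needs more patients.

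**What to change.** 1. In the Sample size section, name Mg vs Mg + H2 (15% vs 5%, two-sided 0.05, unpooled formula) as the comparison behind 413, if the sponsor confirms it.
2. In the Statistical analysis section, fix one procedure for the DCI pairs: either a three-arm chi-square (2 df) at 0.05 followed by each pair at two-sided 0.05, described as a closed test, or Holm. State that chi-square is the pairwise test.
3. State that this controls familywise error over the three DCI pairs only, and say separately how the second primary outcome, vasospasm, is handled.
4. If single-step Bonferroni is kept, restate the power for Mg + H2 vs Mg as about 67% (71% with no loss). Restoring 80% by size instead would need about 184 per arm by the unpooled formula: 552 evaluable, or 552/0.9, about 614, randomised.

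Items 1 to 3 change wording only and add no patients. Their cost is the higher chance of a false claim somewhere across the two primary outcomes, unless item 3 also sets an adjustment across them; such an adjustment would lower the DCI level and so the 82%. The trial is described as ongoing, so the change should be made before unblinding.

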### Statistical analysis

The study design accords to the ‘intention to treat’ principle. A test for overall comparison (e.g. analysis of variance, or if the conditions for analysis of variance are not met, a non-parametric equivalence such as the Kruskal-Wallis test) will be employed for each outcome across all three interventions, and if found to be significant, pair-wise comparisons will be made. We appreciate that many pair-wise comparisons suffer from Type I (false-positive) error, so we will adjust for multiplicity of comparisons by using steps such as Bonferroni and Tukey's procedure. The statistical procedures for pair-wise comparisons will depend on the nature of the data: for example, for dichotomous outcomes, we will use Fisher’s exact test or chi-square test as appropriate, and for continuous outcomes we will use the t-test if the observations in each arm are normally distributed; or the Mann–Whitney U-test if non-normally distributed. A value of p < 0.05 will be considered significant.

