**Discussion:**

The present protocol for a randomized, placebo-controlled study of intravenous hydrogen therapy with intra-cisternal magnesium infusion is expected to establish the efficacy and safety of this therapeutic strategy.

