Increasing evidence has suggested that enhanced oxidative stress is involved in EBI as well as cerebral vasospasm following SAH [26–29]. Hydrogen can selectively reduce hydroxyl radicals and peroxynitrites, which are very strong reactive oxygen species that react indiscriminately with nucleic acids, lipids, and proteins, resulting in DNA fragmentation, lipid peroxidation, and protein inactivation [30–38]. Previous studies have shown that hydrogen has antioxidant, anti-apoptotic, anti-inflammatory, and cytoprotective properties that are beneficial to the cell [30]. Hydrogen is highly diffusible and could potentially reach subcellular compartments, such as the mitochondria and nuclei, which are the primary sites of reactive oxygen species generation and DNA damage [30,38]. In addition, hydrogen has no side effects, and we previously showed that hydrogen can be safely administered intravenously in patients with ischemic stroke [33]. Furthermore, recent experimental studies showed that hydrogen can alleviate EBI after SAH via attenuation of neuronal apoptosis [39–42].

These findings suggest that combination therapy using intravenous hydrogen infusion and intra-cisternal magnesium sulfate infusion may be effective to treat both EBI and delayed cerebral vasospasm. The present randomized controlled clinical trial is intended to investigate the effects of intravenous hydrogen therapy with intra-cisternal magnesium sulfate infusion on the occurrences of cerebral vasospasm and DCI, and clinical outcomes in patients with high-grade SAH.

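### The sample size fits Mg + H2 versus Mg on DCI at an unadjusted 0.05, but the analysis makes that pair one of three equal, adjusted comparisons and ties no hydrogen claim to it

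*Protocol article*

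**What the plan says.** **Sample size** gives three DCI rates: "Assuming that the incidence of DCI is 35% in the control group, 15% in the Mg group" and "5% in the Mg + H_2_ group". From these it states that "a total of 413 patients will be required" ("80% power and 2-sided α = 0.05"), raised to 450 for roughly 10% loss, or 150 per arm. It does not say which comparison was powered.

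**Statistical analysis** sets an overall test that "will be employed for each outcome across all three interventions, and if found to be significant, pair-wise comparisons will be made". The pair-wise tests are to be adjusted for multiplicity, with Bonferroni and Tukey named as examples, and dichotomous outcomes are compared by Fisher's exact or chi-square test. No pair is singled out.

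**Background** describes the trial as "intended to investigate the effects of intravenous hydrogen therapy with intra-cisternal magnesium sulfate infusion on the occurrences of cerebral vasospasm and DCI" and names no comparator. The Discussion, in both the abstract and the main text, says that the study "is expected to establish the efficacy and safety of this therapeutic strategy".

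**The concern.** The three pairs answer different questions. Mg + H2 versus control tests the whole package against placebo, and magnesium alone could win it. Mg versus control tests magnesium. Only Mg + H2 versus Mg isolates hydrogen, and the Background's case for the combination rests on hydrogen: it argues that effective CSF magnesium levels are hard to reach while early brain injury is developing, and offers hydrogen to fill that gap.

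The sizing appears to rest on the hydrogen contrast, which has the smallest assumed difference of the three. The analysis section then gives it no special place and applies an adjustment that the sample size did not allow for. Two things are at stake: the power of the comparison that fixed the size of the trial, and clarity about which result may support a statement that hydrogen adds benefit.

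**Working it through.** **Inputs.** DCI 35% / 15% / 5%, two-sided 0.05, 80% power, 413 evaluable, 450 recruited, about 10% loss (Sample size); 1:1:1 allocation (Randomization). After 10% loss, 450 x 0.9 = 405, or 135 per arm.

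**Step 1: reproduce 413.** Two proportions, unpooled variance, Mg versus Mg + H2:

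n = (1.960 + 0.842)^2 x (0.15 x 0.85 + 0.05 x 0.95) / 0.10^2 = 137.36 per arm; x 3 = 412.07, rounded up to 413. This is an exact match.

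Other bases do not fit:

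| Basis | Total, three arms |
|---|---|
| Mg + H2 vs Mg, pooled variance | 3 x 141 = 423 |
| Mg + H2 vs Mg, continuity-corrected | 3 x 160 = 480 |
| Mg vs control, pooled | 3 x 73 = 219 |
| Mg + H2 vs control, pooled | 3 x 27 = 81 |
| Overall 2-df chi-square | about 93 |

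**Step 2: power for the hydrogen contrast under the stated analysis.** Take Bonferroni over three pairs, 0.05/3 = 0.0167, critical value 2.394. With pooled variance under the null:

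- 150 per arm: null SE = sqrt(2 x 0.10 x 0.90 / 150) = 0.03464; alternative SE = sqrt(0.175 / 150) = 0.03416. (0.10 - 2.394 x 0.03464) / 0.03416 = 0.50, so power is 69.1%.
- 135 per arm: the SEs are 0.03652 and 0.03600. (0.10 - 2.394 x 0.03652) / 0.03600 = 0.35, so power is 63.7%.

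A simulation of the whole sequence at the protocol's rates (200,000 trials; overall chi-square at 0.05, then uncorrected pair-wise chi-square tests) gives slightly higher values than the formula:

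| Rule for pairs | 150 per arm: simulated (formula) | 135 per arm: simulated (formula) |
|---|---|---|
| Bonferroni, 0.0167 | 71% (69.1%) | 67% (63.7%) |
| Each pair at 0.05 after the overall test | 84% (82.6%) | 81% (78.5%) |

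The overall test costs nothing here: its power at these rates exceeds 99.9% at 405 or 450 patients.

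To keep Bonferroni and still reach 80% would take 3 x 183.21 = 549.63, so 550 evaluable patients (unpooled), or 3 x 188 = 564 (pooled). That is 137 to 151 more than 413, before loss to follow-up.

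**Step 3: is the pair-wise adjustment needed behind the overall test?** With exactly three arms, if any two pair-wise null hypotheses are true, all three arms are equal. So only two situations can produce a false rejection:

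- All arms equal: the overall test at 0.05 must be falsely significant first.
- Exactly one pair equal: only one true null exists, and it is tested at 0.05.

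Either way the family-wise error within one outcome is held at 0.05. Simulation agrees. Any false rejection occurs in 0.050 to 0.051 of trials under 35/35/35 and 0.049 under 15/15/15. A false Mg + H2 versus Mg rejection occurs in 0.049 to 0.050 under 35/15/15, and a false Mg versus control rejection in 0.049 to 0.050 under 35/35/5.

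**The case against.** An overall test followed by adjusted pairs is a conventional three-arm plan. A condensed article may leave the ranking of the pairs to an analysis plan that is not shown, so silence about a deciding contrast is not a fault in itself. That stands. What remains is what the article does fix: a sample size matching one contrast at an unadjusted level, beside an analysis that adjusts that contrast.

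A reader might go further and infer that the trial could declare hydrogen effective on a win over control alone, with the choice of contrast made after the data are seen. The documents do not support this. Once the overall test is significant, the pair-wise comparisons are planned together, so the hydrogen pair is tested alongside the others. The Discussion sentence is an expectation, not a decision rule, and no section says that a win over control would be reported as a hydrogen effect. If hydrogen did nothing, Mg + H2 beating control but not Mg would be the correct answer on both pairs, so the frequency of that pattern is not an error rate.

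Mg + H2 versus control is also a valid test of the package against placebo. Requiring the combination to beat both other arms before it is called effective would change the claim rather than protect it.

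**Conclusion.** The point holds in limited form. The contrast that reproduces the sample size is neither named nor protected in the analysis. With Bonferroni over three pairs its power is about 71% (150 per arm) or 67% (135 per arm) by simulation, 9 to 13 percentage points below the stated 80%; by the formula it is 69% and 64%. In addition, nothing links a statement about hydrogen's added benefit to the one pair that can support it.

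This rests on four assumptions:

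- The sizing contrast is inferred from an exact numerical match; the protocol does not state it.
- Bonferroni is one of the two examples given. Tukey was not calculated.
- The pairs are compared by chi-square without continuity correction. Fisher's exact test would be more conservative.
- The DCI rates are the protocol's own.

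**What to change.** In Statistical analysis, before unblinding:

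1. Name Mg + H2 versus Mg on DCI as the contrast that supports any claim that hydrogen adds benefit.
2. State that Mg + H2 versus control tests the whole package against placebo and cannot by itself support a hydrogen claim.
3. For DCI, replace the Bonferroni/Tukey step with a closed procedure: overall three-arm chi-square test at two-sided 0.05, then each pair at two-sided 0.05 only if the overall test is significant.
4. State that a non-significant Mg + H2 versus Mg result will be reported as hydrogen's added effect not shown, not as proof that the effect is magnesium alone.

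Sample size should also say that 413 refers to Mg + H2 versus Mg.

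The cost is a few sentences, with no extra patients or data. There are two downsides. A win over control alone can no longer be presented as evidence for hydrogen. The procedure also controls error only within DCI: cerebral vasospasm is a primary outcome too, and error control across the two outcomes still needs its own rule.

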**Methods:**

This study is a randomized, double-blind, placebo-controlled design to be conducted in two hospitals. A total of 450 patients with high-grade subarachnoid hemorrhage will be randomized to one of three arms: (i) Mg + H_2_ group, (ii) Mg group, and (iii) control group. Patients who are assigned to the Mg + H_2_ group will receive intra-cisternal magnesium sulfate infusion (2.5 mmol/L) at 20 mL/h for 14 days and intravenous hydrogen-rich fluid infusion (200 mL) twice a day for 14 days. Patients who are assigned to the Mg group will receive intra-cisternal magnesium sulfate infusion (2.5 mmol/L) at 20 mL/h for 14 days and intravenous normal glucose-electrolyte solution (200 mL) without added hydrogen twice a day for 14 days. Patients who are assigned to the control group will receive intra-cisternal Ringer solution without magnesium sulfate at 20 mL/h for 14 days and intravenous normal glucose-electrolyte solution (200 mL) without added hydrogen twice a day for 14 days. Primary outcome measures will be occurrence of delayed cerebral ischemia and cerebral vasospasm. Secondary outcome measures will be modified Rankin scale score at 3, 6, and 12 months and biochemical markers.

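### Two primary outcomes are each tested at p < 0.05 with no stated success rule or error control across them; if either one suffices, the family-wise error is up to about 10%, not 5%

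*Protocol article*

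**What the plan says.** - **Two primaries.** Abstract, Methods: "Primary outcome measures will be occurrence of delayed cerebral ischemia and cerebral vasospasm". The Outcome measures section lists the same two.
- **Two definitions of the second primary.** Outcome measures gives "angiographic vasospasm which is defined as moderate-to-severe arterial narrowing on CT angiography and/or digital subtraction angiography" and then, in a separate sentence, "Transcranial Doppler vasospasm which is defined as a mean flow velocity in the M1 of >120 cm/s". No word says how the two definitions combine.
- **One overall test per outcome.** Statistical analysis: a three-arm test "will be employed for each outcome across all three interventions, and if found to be significant, pair-wise comparisons will be made".
- **Adjustment between arms.** The same section: "We appreciate that many pair-wise comparisons suffer from Type I (false-positive) error, so we will adjust for multiplicity of comparisons", with Bonferroni and Tukey as the examples.
- **One threshold.** "A value of p < 0.05 will be considered significant".
- **Sample size on DCI only.** "Assuming that the incidence of DCI is 35% in the control group, 15% in the Mg group, and 5% in the Mg + H_2_ group", and on that basis "a total of 413 patients will be required (80% power and 2-sided α = 0.05").

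No section gives an order of testing, a division of alpha or a both-must-succeed rule for the two primaries.

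**The concern.** The pair-wise adjustment starts only after an outcome's overall test has reached significance. It therefore cannot control the error made across the overall tests that come before it. With two primaries and a full 0.05 on each, a reader cannot tell what result makes the trial positive. If either primary suffices, the nominal 5% does not hold for the main conclusion.

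The Discussion expects the trial to establish efficacy, and it presents the treatment of vasospasm as a route to preventing DCI. Under an either-one rule, an efficacy claim could rest on vasospasm alone, with no difference in DCI and with more than a 5% chance that the claim is false.

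**Working it through.** **Inputs from the article.** Two primary outcomes; one overall test each; threshold 0.05; adjustment for pairs of arms; DCI rates of 35%, 15% and 5%; two-sided α = 0.05; 80% power; 150 per arm.

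**Step 1: reproduce the sample size.** The article does not say which comparison gave 413. Comparing 15% with 5% by the normal formula with unpooled variance:

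n per arm = (1.960 + 0.842)² × (0.15 × 0.85 + 0.05 × 0.95) / 0.10² = 7.849 × 0.175 / 0.01 = 137.36

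3 × 137.36 = 412.07, rounded up to 413. This matches. The pooled-variance version gives 141 per arm, 423 in total. The stated size is therefore consistent with the whole 0.05 being spent on a DCI comparison, with nothing reserved for vasospasm.

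**Step 2: family-wise error for two primaries, if either suffices.**

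- Independent: 1 − 0.95² = 0.0975.
- Upper bound under any dependence: 0.05 + 0.05 = 0.10.
- Correlated test statistics (bivariate normal): 9.5% at correlation 0.3, 9.1% at 0.5, 8.3% at 0.7. Repeating this with 2-df statistics, as in a three-arm test, gives 9.1 to 9.2% at 0.5 and 8.4 to 8.5% at 0.7.
- Simulated binary outcomes (150 per arm, three-arm chi-square test, no effect on either outcome, 20,000 runs per setting): 9.2% to 10.0% for latent correlations from 0 to 0.9. The rates of 35% for DCI and 70% for vasospasm are assumptions. The simulation standard error is √(0.0975 × 0.9025 / 20,000) = 0.2 percentage points, so the highest values do not differ from 9.75%.

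Correlation lowers the simulated figure little because a 35% and a 70% outcome cannot be closely correlated as yes/no variables. A latent correlation of 0.9 gave an observed correlation of only 0.47.

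**Step 3: if both must succeed.** When neither outcome is affected, both tests must reject, which happens at most 5% of the time. There is no inflation.

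**Step 4: if the two vasospasm definitions were separate primaries.** Independent: 1 − 0.95³ = 0.1426. Upper bound: 0.15. Simulated with correlation (third rate of 60% assumed): 12.5% to 14.0%.

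**Step 5: possible remedies.**

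| Rule | Family-wise error, overall tests | Consequence |
|---|---|---|
| DCI at 0.05, then vasospasm at 0.05 only if DCI is significant | at most 5% | no change in N |
| 0.025 on each primary | 1 − 0.975² = 4.94% if independent, at most 5% | power for 15% vs 5% at 150 per arm falls from 82.6% to 74.4%; 80% needs about 500 to 510 evaluable patients instead of 413 |
| Both must succeed | at most 5% | the article gives no vasospasm rates, so power is unknown |

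At the planning rates the overall DCI test has more than 99.9% power even with 405 patients (450 less 10%). The gate in the first row would then rarely block vasospasm.

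**The case against.** The strongest reply is that this is an article condensing a protocol. The success rule, the handling of alpha across outcomes and the way the two vasospasm criteria combine may all stand in an analysis plan that is not shown. The Statistical analysis section is also worded by example in several places. This stands in part: one can say only that the article states no control, not that none exists anywhere. It does not remove the point, because the article positively fixes a test per outcome, a single 0.05 threshold and an adjustment introduced for pairs of arms. Followed as written, those three do not hold 5% across the primaries.

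The phrase about multiplicity of comparisons could be stretched to cover outcomes. However, the same sentence ties it to pair-wise comparisons, and Tukey's procedure compares groups.

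Three stronger readings are tempting, and the document does not support them:

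- **That the error is doubled as a matter of fact.** This needs an either-one success rule. The article states no such rule, and under a both-must-succeed rule there is no inflation.
- **That there are three primary tests and a 14.3% error.** Both definitions stand under one listed outcome, occurrence of cerebral vasospasm, so one outcome with two criteria is a natural reading. The 14.3% also assumes independence, although both definitions aim at the same phenomenon.
- **That daily bilateral Doppler readings produce many false positives and so inflate the error.** The article gives no error rate per reading, and repeated readings in one patient are not independent. Misclassification that is equal across blinded arms dilutes an effect; it does not raise the type I error.

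**Conclusion.** The point holds in a bounded form. The article names two primaries, gives each the full 0.05, adjusts between arms within an outcome, and leaves the success rule open. On the assumption that either primary suffices, the family-wise error is 9.75% if the outcomes are independent, about 8 to 9% at correlations of 0.5 to 0.7, and never above 10%, against the stated 5%. Near-complete overlap of the outcomes would bring it towards 5%. A figure of up to 14 to 15% would need the further assumption that the two vasospasm definitions are tested as separate primaries. All these figures concern the overall tests when the treatments have no effect on any of the outcomes.

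**What to change.** Before unblinding, amend the protocol and registry entry to state the following:

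1. DCI, the outcome used for the sample size, is tested first with the overall three-arm test at two-sided 0.05.
2. Vasospasm is tested confirmatorily at 0.05 only if the overall DCI test is significant. Otherwise its result is descriptive.
3. The confirmatory vasospasm test uses the angiographic definition. Doppler vasospasm is supportive.
4. The pair-wise adjustment within each outcome stays as planned.

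This holds 5% for the two overall tests with no change in N. It does not hold 5% jointly for every pair-wise claim in both outcomes. If two arms are equal on DCI and the third differs, the equal pair is tested at 0.05 / 3 = 0.0167 under Bonferroni and vasospasm at 0.05, so the bound is 0.0167 + 0.05 = 0.067. The amendment should say that control is at the level of the overall tests.

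The costs are an amendment to an ongoing trial, with a record that it was made while still blinded, and the loss of any confirmatory claim for a vasospasm effect without a DCI effect. If the sponsor prefers to keep two equal primaries, an even split of alpha or an explicit both-must-succeed rule would also hold 5%, at the price in power shown in the table or with power unknown for vasospasm.
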